#### Statistical analysis

The SPSS 19.0 statistical software package will produce the statistical analysis of the study. With the aid of Shapiro–Wilk test, the normal deviation of cycles to failure, failure load and axial construct stiffness in each group will be monitored. To screen the fluctuation in the parameters of interest, the Levene test will be utilized. Any major difference between the two implants will be registered with paired-samples *t* test, while we set a *p* = 0.05 as level of significance.

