#### Preparation of specimens

Eight synthetic composite osteoporotic femurs of medium size (model: 3503; SawBones Worldwide, WA, USA) with 10 PCF low-density cancellous, thin-walled low-density cortical shell and 16 mm hollow canal, would be randomly assigned to two groups (*n* = 4 in each group) to receive either a classic Gamma3 or an IT nail. Two additional specimens will be kept intact and will be served as reference for system calibration and material properties validation. The use of sawbone models with validated mechanical properties [34–36] was preferred instead of cadaveric bones to eliminate size, geometry and mechanical variability between specimens thus increasing stanchness of our numerical analysis due to the availability of the finite element 3D digital file with coded material properties of our specimen (Femur, Finite Element Model of #3503, SawBones Worldwide, WA, USA).

The instrumentation of Gamma3 and IT will be applied in a standard manner, according to the manufacturer’s manual, first on the intact sawbones (prior to fracture creation) under image intensifier using antero-posterior and lateral imaging to ensure proper implant position and a tip-to-apex distance (TAD) < 20 mm (Fig. 1a–c).

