#### Loading scheme

Once the implants were settled well and distal ends were embedded, the two groups of model bones were fixed on the biomechanical test machine (MTS 647, hydraulic wedge grip) (Fig. 2f). Initially, all specimens will be subjected to an axial pressure of 100–200 N for 10 cycles with a loading rate of 1 Hz to eliminate creeping effect.

Axial cycling load compression will be applied to simulate the stress experienced by a patient with 70 kg body weight at 4–6 weeks postoperatively [38, 39]. Firstly, the axial compression test is carried out under cyclic loading, with an initial load of 400 N, incremental load of 100 N, and maximum load set to 1400 N, divided into 10 subgroups; each subgroup will be conducted in a cycle of 10,000 times, respectively, with a loading rate of 1 Hz. After the cyclic test, the average fracture gap movements will be recorded. A torsional test will follow with the following parameters: Starting from 0°, the maximum torsion angle will be set to 3° with a loading rate of 0.1°/s. Torque at the angle of 1°, 2°, 3° will be recorded, respectively. Finally, an axial compression failure test will be performed with a loading rate of 4.6 mm/s continuously, until fatigue failure; the latter is defined as fracture gap > 20 mm, nail cutting‐out or breakage and fracture line found near the distal locking screw.

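### The bench study randomises eight unmatched femurs 4 versus 4 but names a paired-samples t test, which does not fit the design and costs half the degrees of freedom

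*Protocol article*

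**What the plan says.** Under Preparation of specimens, the protocol article describes "Eight synthetic composite osteoporotic femurs of medium size" that "would be randomly assigned to two groups", n = 4 in each, "to receive either a classic Gamma3 or an IT nail". Two further femurs stay intact for calibration and are not part of the comparison. No block, left/right match or crossover of implants is described.

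Under the Statistical analysis heading of the biomechanical study, "the normal deviation of cycles to failure, failure load and axial construct stiffness in each group will be monitored" by the Shapiro–Wilk test. Levene's test follows, and then: "Any major difference between the two implants will be registered with paired-samples" t test, with "0.05 as level of significance".

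The Loading scheme section sets the cyclic phase as "initial load of 400 N, incremental load of 100 N, and maximum load set to 1400 N, divided into 10 subgroups", each of 10,000 cycles at 1 Hz. A torsional test to 3° comes next, and finally a continuous compression test to failure.

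**The concern.** A paired t test analyses within-pair differences, so each Gamma3 value must belong with one particular InterTan value. Here no Gamma3 femur is linked to any InterTan femur. The synthetic bones were chosen precisely to remove variation between specimens, which takes away the usual reason to pair. The rest of the same paragraph (normality within each group, Levene's test) belongs to a comparison of independent groups, and the clinical part uses an independent-samples t test for its own two-group comparison.

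Bench testing is the first stated aim, with a hypothesis of higher stiffness and failure load for InterTan. With four femurs per group, avoidable loss of power matters. A pairing that is nowhere defined also leaves an analytic choice open until after the data are seen.

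Two smaller mismatches sit alongside. Cycles to failure is listed for analysis although every femur is put through the same fixed cyclic programme. And the stated number of load subgroups does not obviously match the stated load range.

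**Working it through.** The protocol gives no power, SD or effect size for the bench study, so there is no figure of its own to reproduce.

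**Inputs.** From the protocol: n = 4 per group, one implant per femur, significance level 0.05. Assumed here: two-sided testing, normal outcomes with equal SD σ, uncorrelated femurs, and true differences of d = 2 and 2.5 SD.

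**Degrees of freedom and critical values**
- Paired: 4 − 1 = 3, critical |t| = 3.182.
- Independent, pooled: 4 + 4 − 2 = 6, critical |t| = 2.447.
- Ratio: 3.182 / 2.447 = 1.30.

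**Precision.** With uncorrelated femurs the true standard error of the mean difference is the same for both tests: σ√(2/4) = 0.707σ. Pairing therefore gains nothing to set against the lost degrees of freedom. The expected 95% CI half-width is critical t × expected sample SD factor × 0.707σ:
- Paired: 3.182 × 0.921 × 0.707σ = 2.07σ.
- Pooled: 2.447 × 0.959 × 0.707σ = 1.66σ.
- The paired interval is about 25% wider.

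**Power.** The paired and pooled figures use the noncentral t with noncentrality d√(4/2) = 1.414d. The Welch and permutation figures are from 200,000 simulated data sets.

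| Test | d = 2 SD | d = 2.5 SD |
|---|---|---|
| Paired (3 df) | 49% | 66% |
| Independent, pooled (6 df) | 66% | 84% |
| Independent, Welch | 61% | 79 to 80% |
| Exact permutation | 49% | 68% |

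The difference detectable with 80% power is 3.01 SD paired and 2.38 SD pooled.

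The permutation row follows from there being C(8,4) = 70 possible allocations. The smallest two-sided p is 2/70 = 0.029 and the next is 4/70 = 0.057, so p < 0.05 is reached only when the two groups separate completely.

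**Dependence on the pairing.** Four femurs per group can be paired in 4! = 24 ways. A made-up example: Gamma3 900, 1000, 1050, 1150; InterTan 1050, 1150, 1250, 1350. The mean difference is 1200 − 1025 = 175 under every pairing.
- Paired in the order listed, the differences are 150, 150, 200, 200; SE 14.4, t = 12.1, p = 0.001.
- Paired in the reverse order, they are 450, 250, 100, −100; SE 116.4, t = 1.50, p = 0.23.
- The pooled independent test gives a single p = 0.079.

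In 2,000 simulated data sets, the verdict at 0.05 changed with the pairing in about 24% when there was no true difference and about 66% when it was 2 SD. With one pairing fixed beforehand, the paired test rejected in about 5% of null data sets.

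**Cycles to failure.** The sequence is a fixed cyclic programme, then torsion, then a continuous failure test. A femur that survives the cyclic phase has only the programme's total as its count, so its cycles to failure are right-censored there. A femur that fails during cycling has a true count but no later torque or failure-test result.

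**Load levels.** 400, 500, …, 1400 N is (1400 − 400)/100 + 1 = 11 levels, separated by ten increments. At 10,000 cycles each and 1 Hz, 11 levels are 110,000 cycles (30.6 h) and ten are 100,000 cycles (27.8 h).

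**The case against.** The strongest reply is that 'paired' is a one-word slip. The per-group normality check, Levene's test and the clinical part's independent-samples test all suggest that the authors had an unpaired comparison in mind. That is plausible, but the document names a specific test and that name needs correcting. Instrumenting each femur before and after the cut does not rescue it, because each femur carries only one implant type.

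A reader might infer that the bench result would be decided by specimen order. The document does not support that: the mean difference does not depend on the pairing, and a pairing fixed beforehand, for example by specimen number, keeps the type I error near 5%. The inflation risk arises only if the pairing is chosen after seeing results. The p values in the made-up example illustrate the mechanism and are not a property of this trial.

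The gain from changing the test should also not be overstated. Welch recovers less power than the pooled test, and an exact permutation test has about the power of the paired test.

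On the side points, it is tempting to say that the experiment does not produce cycles to failure at all. It can, for any femur that fails during cycling; the problem is censoring, and how much depends on failure rates the protocol does not give. Likewise, ten subgroups may mean ten increments after the initial load, so the wording is ambiguous rather than shown to be wrong. If every femur gets the same regimen, it does not bias the group comparison.

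**Conclusion.** The concern holds for the bench study. The named test contradicts the randomised, unmatched design. Its cost is half the degrees of freedom, a confidence interval expected to be about 25% wider than the pooled one, and a p value that depends on an undefined pairing. Against the paired test, power at 2 and 2.5 SD rises by roughly 17 and 18 percentage points with the pooled test, and by roughly 12 and 13 to 14 with Welch. These figures rest on assumed effect sizes, normality, equal SD, two-sided testing and uncorrelated femurs.

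The handling of cycles to failure and the count of load levels are secondary points of clarification. None of this touches the clinical trial, whose Harris and Oxford hip scores are already compared with an independent-samples t test.

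**What to change.** - In the bench Statistical analysis section, replace the paired-samples t test with an independent-samples t test. State in advance whether it is pooled or Welch, and report the mean difference with its 95% CI.
- If an exact permutation test is added as a check, note that at four per group it reaches p < 0.05 only with complete separation.
- If pairing was really intended, say how pairs are formed and randomise within them.
- Treat cycles to failure as right-censored at the end of the cyclic programme, or drop it. Keep axial stiffness and failure load, which carry the stated hypothesis. Do not substitute a cyclic load level for the load from the continuous failure test, since they are different quantities.
- Reconcile the ten subgroups with the 400 to 1400 N range.

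The cost is protocol wording only; no extra specimens are needed.

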### Finite element analysis (FEA)

Finite element analysis of the implanted sawbones will be performed using the ANSYS v.19.2 commercial FE code (ANSYS inc. Cannonsburg, Pennsylvania, USA). The femoral geometry model will be obtained by the manufacturer (3D CAD digital file with coded material properties, Sawbones, Vashon Island, Washington, USA). The geometrical features of each implant (Gamma3 and IT) will be characterized following 3D CT scanning. Only the basic geometrical features will be modeled using FEA, since it has been recognized that several additional details (i.e., threads of the lag screw(s) or distal interlocking screw) significantly complicate the analysis, without affecting considerably the computed stress and strain fields [40].

Sawbones geometry will be imported in the ANSYS FE code and the fracture plane will be modelled by creating a proper surface that divide the cortical and cancellous volumes of the bone for the unstable fracture cases. The native neck shaft angle and the anatomic reduction angle will be 135°. A central position of the hip screw with a TAD of 16–18 mm and a minimum of 2 mm width of cancellous bone between the hip screw and the femoral cortex will be applied. Several FEA models will be created with the aim to study different scenarios of reduction (in varus or valgus) as well as inappropriate lag screw positions as illustrated in Fig. 3. Our hypothesis is that even with inappropriate reduction or lag screw(s) mispositioning the biomechanical properties of IT will be better than Gamma3.

**Fig. 3 Fig3:**
[figure not shown]
Several FEA models will be created with the aim to study different scenarios of reduction (in varus or valgus) as well as inappropriate lag screw positions

As has been proposed in a similar study [40], the developed geometries will be meshed using tetrahedral elements with an optimal element size of 3 mm as this leads to acceptable results regarding accuracy, without significantly increasing the computational cost. Appropriate linear elastic, isotropic and homogeneous material properties will be assigned to the several parts of the FE model, based on the data provided by the manufacturers. The longitudinal Young’s modulus for the cortical bone (82 pcf fiber filled epoxy) is E_cortical_ = 5.2 GPa, and for the cancellous bone (10 pcf solid foam) E_cancellous_ = 58 MPa, while for the Gamma3 and IT the titanium alloy the Young’s modulus is E_material_ = 116 GPa. For the modeling of the distal femoral fixation during the experiments, fully fixed boundary conditions will be applied on the FE models surface nodes situated at the lower 130 mm of the femur model. A constant vertical force of 1000 N will be applied on the top of the femoral head; as a linear-elastic FE analysis will be considered, the calculated results will be derived for other load values using linear interpolation or extrapolation. Linear regression modeling will be utilized in order to associate a set of independent variables or predictors (implant type, lag screw(s) positioning and reduction angle) with any measurement outcome, also referred to as the dependent variable or target, separately. For each model, the beta estimates and the *p* values will be returned, among others. Statistical significance was taken when *p* < 0.05.

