## Materials and methods

### Biomechanical study

#### Implants

The experimental work will be undertaken in the Laboratory of Technology and Strength of Materials at the Department of Mechanical Engineering and Aeronautics of Patras University. Two implant systems will be compared against biomechanical testing, the classic Gamma3 and the InterTan nail (IT).

The Gamma3®nail (Stryker, Mahwah, NJ, USA) that would be used in the current study has a length of 180 mm, 11 mm nail diameter and 130° neck-shaft angle and utilizes a single lag screw with a standard diameter of 10.5 mm. The Trigen Intertan (Smith + Nephew, Watford, UK) nail is a current generation IM device, featuring a dual lag screw configuration comprised of a 11.0 mm superior lag screw and a 7.0 mm smaller integrated screw that allows for linear compression of the fragments at the fracture site while providing high rotational stability [32, 33]. The proximal part of the nail has a trapezoid design that provides a pressfit fixation in the metaphyseal region thus positioning more material on the lateral side of the nail where tensile/stretching forces tend to be greatest. Finally, the “clothes pin” distal tip provides less rigidity to decrease the stress riser and reduce the incidence of anterior thigh pain. An 11 mm nail with a 130° neck-shaft angle will be used for the present study.

We would hypothesize that the above variations, may create differences in strain distribution and thus dissimilar biomechanical behaviors of these two nails. The main hypothesis of our biomechanical study is that the InterTan nail would provide higher stiffness and load to failure and less varus collapse in unstable intertrochanteric fractures (AO/OTA A2). The transmission of forces as measured by cortical surface-strain distribution in the proximal femur will be evaluated using digital image correlation (DIC) and classic strain gauges.

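### The 3 mm finite element size is taken from another study, and adequate resolution at the screw-bone interface (2 mm layers, a 7.0 mm screw) is not shown for these models

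*Protocol article*

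**What the plan says.** All places are in the protocol article.

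- **Mesh.** After Fig. 3, the FEA section reads "As has been proposed in a similar study [40], the developed geometries will be meshed", and specifies that they will be "meshed using tetrahedral elements with an optimal element size of 3 mm as this leads to acceptable results regarding accuracy". Modest computing cost is the other reason given. Element order, local refinement and a convergence result for these geometries are not stated.
- **Thin layer.** The same section, before Fig. 3, specifies a centrally placed hip screw and "a minimum of 2 mm width of cancellous bone between the hip screw and the femoral cortex will be applied". It also plans models with varus or valgus reduction and badly placed lag screws.
- **Screws.** Under Implants, the Gamma3 "utilizes a single lag screw with a standard diameter of 10.5 mm", while the InterTan has "a 11.0 mm superior lag screw and a 7.0 mm smaller integrated screw".
- **Geometric detail.** "Only the basic geometrical features will be modeled using FEA"; screw threads, for example, are left out.
- **Bone model.** Preparation of specimens describes a "thin-walled low-density cortical shell and 16 mm hollow canal". The shell thickness is not given.
- **Role and validation.** The aims in the Introduction say that computed surface strains will be validated against the bench tests. The models will then assist the nail comparison by supplying internal stress and strain fields that the bench cannot measure.
- **Analysis.** The FEA section regresses each outcome on implant type, lag screw position and reduction angle, and reports coefficients and p values.

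**The concern.** The stated element size exceeds the smallest bone dimension that the same section permits, and it is coarse relative to one of the three screws. The thin layer is also where steep gradients are to be expected: by the section's own moduli, soft foam lies between a much stiffer screw and a much stiffer cortex.

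Two features of the plan make this matter.

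- **The validation does not reach the region.** Strain gauges sit 2 cm below the fracture line and 2 cm below the distal locking screw, and digital image correlation (DIC) reads the outer surface of the proximal femur. Neither observes the strain inside the head around the screws.
- **One hypothesis rests on the models alone.** The FEA section expects the InterTan to do better even when reduction or screw position is poor. The eight implanted bench specimens are all to be instrumented with proper position, so no bench test of malposition is described.

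The 7.0 mm screw exists in only one implant, and the layer thickness can change with screw position. Discretisation error may therefore be correlated with the regression predictors and be read as an effect of implant or position.

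**Working it through.** **Inputs.** Element size h = 3 mm, minimum cancellous layer 2 mm, and moduli of 116 GPa (titanium alloy), 5.2 GPa (cortical) and 58 MPa (cancellous), all from the FEA section. Screw diameters of 10.5, 11.0 and 7.0 mm, from Implants.

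**The plan's own figure.** The 3 mm size comes from a cited study and has no derivation in the article, so there is nothing to reproduce.

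**Step 1: nominal elements across each feature, d / h.**

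| Feature | d (mm) | d / 3 |
|---|---|---|
| Minimum cancellous layer | 2 | 0.67 |
| InterTan integrated screw | 7.0 | 2.33 |
| Gamma3 lag screw | 10.5 | 3.50 |
| InterTan lag screw | 11.0 | 3.67 |

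The cortical shell cannot be added because its thickness is not given.

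**Step 2: stiffness contrast at the thin layer.**

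- Screw to foam: 116,000 / 58 = 2,000.
- Cortex to foam: 5,200 / 58 ≈ 90.

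**Step 3: how unequal the geometric error could be.** Assume straight-sided elements with edges of about 3 mm, so that a round screw becomes a regular polygon inscribed in its circle. The number of edges is about πd / 3. Relative to the true circle, the bending inertia is

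[(n/24) · sin(2π/n) · (2 + cos(2π/n))] / (π/4).

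| Screw | πd / 3 | n | Ratio |
|---|---|---|---|
| InterTan 7.0 mm | 7.33 | 7 to 8 | 0.76 to 0.81 |
| Gamma3 10.5 mm | 11.0 | 11 | 0.90 |
| InterTan 11.0 mm | 11.52 | 11 to 12 | 0.90 to 0.91 |

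Under this assumption the small InterTan screw would lose about 19 to 24% of its bending inertia, and each of the larger screws about 9 to 10%. Curved quadratic elements or local refinement would make this error much smaller. The article does not say which will be used.

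**Step 4: local size needed in a 2 mm layer.** For k elements across, h = 2 / k. If that size were used everywhere, the element count would rise by (3 / h)³.

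| k | h (mm) | Count factor if uniform |
|---|---|---|
| 1 | 2.0 | 3.4 |
| 2 | 1.0 | 27 |
| 3 | 0.67 | 91 |

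Uniform refinement is therefore expensive, which is why the remedy should be local.

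**The case against.** The strongest reply is that a nominal size is not a mesh. A mesh that conforms to separate screw, cancellous and cortical volumes must place at least one element in a 2 mm layer, so 0.67 is a ratio and not a count of elements. Element order and refinement may be in the fuller finite element plan, and a condensed article may properly omit them. The cited study may have tested convergence on comparable geometry, which cannot be judged here. All of this stands. A reader might infer that the fields around the screws are unresolved, but the article does not establish that.

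Further limits also stand:

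- The 2 mm value is a floor at the tightest place and does not describe the layer in general. If one assumes that a tip-to-apex distance of 16 to 18 mm is shared equally between two views, 8 to 9 mm of bone lies ahead of a central tip, or 2.7 to 3.0 nominal elements.
- A reader might suppose that malpositioned screws leave less than 2 mm. No text says so, and the figure of those scenarios is not available.
- The validation is not confined to the shaft, since DIC covers the proximal femur.
- The InterTan's main lag screw is resolved about as well as the Gamma3 screw (3.67 against 3.50). Only its second screw is coarser, and no direction or size of bias in a bone strain has been shown.

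These replies do not remove the core of the point. The article states a size and calls it optimal for these geometries without a basis in them. One element across a soft layer between two stiff bodies represents the through-thickness gradient poorly. Surface strain, even proximal, is not internal strain.

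**Conclusion.** The point holds in a limited form: adequate resolution at the screw-bone interface is not shown, and the planned validation would not reveal a shortfall there. The nominal figures are 0.67 elements across the thinnest permitted layer, and 2.3 across the small InterTan screw against 3.5 across the Gamma3 screw. The loss of bending inertia (about 19 to 24% against about 10%) illustrates how the error could differ by implant. It depends wholly on the assumption of straight-sided elements at the nominal size.

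A reader might conclude that these fields settle which nail is better. The Introduction says only that they assist a comparison that also rests on direct tests of stiffness and failure load. The malposition hypothesis is the part that leans most on the models. Nothing in the randomized trial's outcomes, sample size or analysis depends on the mesh.

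**What to change.** Keep 3 mm as the global size and add four statements to the FEA section:

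1. The mesh will be refined locally around the lag screw(s) and the thin cancellous layer. A local size of 1 mm, giving two elements across 2 mm, is a possible start, but the convergence check should settle the value.
2. Convergence will be checked for each implant and for the scenario with the thinnest layer.
3. The tolerance will be set in advance. One example is that peak bone strain changes by less than 5% when the local size is halved. The 5% is a suggestion and does not come from the article.
4. The same converged settings and element type will be used in every scenario, so that coefficients for implant and position are not mixed with mesh differences.

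If the full finite element plan already contains these steps, a sentence saying so is enough. The cost is more computing time for models that are linear-elastic. No new specimens or bench tests are needed.

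### Finite element analysis: p values and a 0.05 threshold are attached to deterministic model output, and the implant coefficient as listed averages over scenarios that the hypothesis takes one by one

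*Protocol article*

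**What the plan says.** The relevant text is the Finite element analysis (FEA) section of the Protocol article, including the paragraph after Fig. 3.

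- **Model inputs.** The femur geometry is the manufacturer's CAD file. Materials are linear elastic, isotropic and homogeneous, with fixed moduli (5.2 GPa cortical, 58 MPa cancellous, 116 GPa implant). The distal end is fully fixed, and one constant vertical force of 1000 N is applied. For other loads, "the calculated results will be derived for other load values using linear interpolation or extrapolation". No input is declared random.
- **Scenarios.** The text speaks of several models covering varus or valgus reduction and inappropriate lag screw positions, and refers to Fig. 3, which is not available to us.
- **Analysis.** "Linear regression modeling will be utilized in order to associate a set of independent variables or predictors", listed as "implant type, lag screw(s) positioning and reduction angle) with any measurement outcome", one outcome at a time. For each model "the beta estimates and the *p* values will be returned, among others". The decision rule is: "Statistical significance was taken when *p* < 0.05".
- **Hypothesis.** It is that "even with inappropriate reduction or lag screw(s) mispositioning the biomechanical properties of IT will be better than Gamma3".

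**The concern.** A p value compares an estimate with the scatter expected from sampling. A linear-elastic model with fixed inputs has no such scatter: running the same scenario again returns the same number. What the regression treats as error is the part of a smooth response that the chosen terms do not capture. A result labelled significant at 0.05 therefore has no 5% error rate behind it. Its size reflects how many scenarios were modelled and how they were coded.

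There is also a mismatch with the question. The hypothesis is about the ranking of the nails when reduction or screw position is poor. A single implant coefficient answers that only if the implant difference is the same in every scenario, and that is the very thing being asked.

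At stake is the third strand of evidence on the two nails. The Introduction lists the finite element work among the study's aims and intends it to assist the comparison of the implants. A favourable average with a small p value could be read as confirmation across malpositions when it is not.

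**Working it through.** The plan gives no sample size, effect size or number of scenarios for this regression, so there is no figure to reproduce. The check is a numerical illustration; every response value in it is assumed.

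**Set-up.** Let x be screw position and a reduction angle, each scaled from -1 to 1, and let I = 0 for Gamma3 and 1 for InterTan. Assume the noise-free response y = 100 + 12x² - 10a + 6a² + 4xa - 4·I, with lower values better. Fit y on I, x and a by ordinary least squares over a full grid for both nails. With n runs, q fitted coefficients and a balanced design, SE(implant) = 2·√(RSS/(n - q))/√n.

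**1. The residual is lack of fit.** On a 3 × 3 grid for two nails (18 runs), the part the straight lines miss is 12(x² - 2/3) + 6(a² - 2/3) + 4xa. Its sum of squares per nail is 144·2 + 36·2 + 16·4 = 424, so RSS = 848 for both. None of this is sampling error: adding the x², a² and xa terms brings RSS to zero apart from rounding (6 × 10⁻²⁶).

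**2. More scenarios, same estimate.** For 18 runs, SE = 2·√(848/14)/√18 = 3.67, t = -1.09 and p = 0.29. Finer grids give:

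| Runs | Estimate | p |
|---|---|---|
| 8 | -4.0 | 0.37 |
| 18 | -4.0 | 0.29 |
| 32 | -4.0 | 0.11 |
| 50 | -4.0 | 0.028 |
| 98 | -4.0 | 0.0006 |
| 162 | -4.0 | 0.000003 |

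**3. Repetition that adds nothing.** Entering the same 18 runs k times gives SE = 2·√(848k/(18k - 4))/√(18k), that is 3.67, 2.43, 1.94 and 1.48 for k = 1, 2, 3 and 5. The p values are 0.29, 0.11, 0.045 and 0.008, although nothing has been learned.

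**4. Coding.** Take the same 18 runs with x and a entered as three-level factors. Only the xa part is now missed, so RSS = 2·64 = 128 on 18 - 6 = 12 degrees of freedom. SE = 2·√(128/12)/√18 = 1.54, t = -2.60 and p = 0.023, against 0.29 with straight lines. The estimate is still -4.

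**5. Average against scenario.** Let the implant difference instead be d = -6 + 10|x| when a < 0, and -6 otherwise. On a 7 × 7 grid (98 runs), the mean of |x| is 4/7 and 3/7 of the angles have a < 0, so the average difference is -6 + 10·(4/7)·(3/7) = -3.55. The regression without interactions returns exactly that, with p = 0.0097 in favour of InterTan. Yet d is positive wherever |x| > 0.6 and a < 0: 4 positions × 3 angles = 12 of 49 scenarios, with d as high as -6 + 10 = +4. Those are malpositions of the kind the hypothesis is about. When d varies in this way, the average also depends on the scenario mix: it is -1.00 with 8 runs, -3.78 with 18, -2.67 with 32 and -3.60 with 50.

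**The case against.** Several points on the other side are fair.

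- **The scenario set may be fixed.** A reader might infer that the analysts can add models until p falls below 0.05. The text points to Fig. 3, which is not shown and may list the scenarios, so the document does not support that inference. A fixed list would settle n, but it would not create sampling error.
- **Interactions are not ruled out.** A reader might infer that the plan commits to main effects only. It does not say so: it lists predictors without a model equation, and a condensed article may leave such terms to a fuller document. What can be said is that no interaction or within-scenario contrast is named, so the regression as listed gives an average.
- **Scaled loads.** A reader might infer that results rescaled to other loads would be entered as extra observations. The article says only that they will be derived.
- **Magnitude.** The p values above rest on an assumed surface, range and coding, and other choices change them greatly. With only several models, a small p value might never arise. Only the direction carries over: with surface and coding held fixed, p fell as scenarios were added in each case tried. That a p value might come out large does not give it a meaning.
- **Reach.** This is an ancillary simulation, and part of the right benchmark is already planned: computed strains are to be validated against bench measurements.

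None of these gives p < 0.05 an error rate on output without a random input.

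**Conclusion.** The point holds for the finite element part. As described, the output is deterministic, so the p values and the 0.05 rule have no sampling interpretation. They depend on the number and coding of scenarios, while the estimated implant difference need not change at all. As listed, the predictors yield an implant coefficient averaged over scenarios, which does not by itself address a hypothesis about each malreduction or malposition.

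The conclusion rests on the article's description of the model having no random input; if material, load or position were in fact sampled from distributions, it would need revisiting. No numerical size can be given for this study, because the scenarios and responses are not stated. A reader might infer that the randomised comparison is weakened too. It is not: the clinical trial's sample size, test levels and primary analyses do not use these regressions.

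**What to change.** In the Finite element analysis (FEA) section:

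1. Remove the p values and the 0.05 threshold for finite element output.
2. Report the InterTan minus Gamma3 difference, absolute and in percent, for each modelled scenario, with its range over scenarios. State in how many scenarios the direction is reversed.
3. Read those differences against the disagreement between computed and bench-measured strains, from the validation already planned in the Abstract (Methods) and the Introduction. Note that the bench specimens are instrumented in proper position, so this benchmark is less direct for malpositions.
4. If a regression is kept as a summary, report coefficients only. Include implant-by-position and implant-by-reduction terms where the scenario set allows.

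The cost is a change of wording, a longer results table and the loss of any significance statement for this part. No new model runs are needed, provided each scenario is run with both nails, as the hypothesis implies. A mesh convergence study would be a useful addition but would need extra runs; the fix does not depend on it.
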